## Results

### Timeline

Enrollment and data collection for phase 1 is expected to conclude by December 2018. Data transcription and analysis will begin in January 2019. For phase 2, 2 clinical trials have been identified for a potential partnership, and these sites have modified their Institutional Review Board protocols to include the addition of teleconsent. Phase 2 will also begin in January 2019. We anticipate reporting results in June 2019 through professional presentations and publications. Study findings will be disseminated through publications, direct update to Community Board Members, and electronically to participants.

### Dissemination

The results of the work from the above aims will be disseminated, throughout the Clinical Translational and Science Award (CTSA) consortium and the broader translational research community, through presentations at national meetings, such as the American Medical Informatics Association Translational Science Summit, relevant CTSA domain task force or interest group meetings, and through publication in peer-reviewed journals. The initial strategy for teleconsent is dissemination through academic research organizations in regional MUSC collaborations, including the Carolinas Collaborative and Mid-South Clinical Data Research Network. The teleconsent underlying framework, Doxy.me is a freely available lightweight telemedicine framework, which will facilitate the dissemination across the CTSA network.

## Discussion

Telemedicine is an innovative health care delivery model that provides care to patients at a distance using telecommunications capabilities [29]. Telemedicine has gained substantial support in recent years as an acceptable care methodology, with effective utilization in many clinical domains that has the potential to overcome several gaps and barriers in clinical trial enrollment by having the ability to remotely recruit and consent potential research participants, especially rural participants who are outside the proximity of the study team. Thus, teleconsent offers a convenient and complementary solution for researchers to meet with prospective participants and obtain consent. Researchers at the MUSC, partnered with the UNC, are interested in building off preliminary research focusing on the teleconsent software, Doxy.me, through a 2-part study.

In phase 1 of this study, participants will be recruited; participants will be residents of South and North Carolina (N=80; 40 from each respective site) from various backgrounds; however, all will meet the inclusion criteria specific to this study. Participants will be walked through the teleconsent process using a mock consent form and then interviewed to determine the overall themes regarding issues such as software difficulties and privacy issues. Results from this part of the study will be used to provide feedback to developers at the MUSC and address potential issues before phase 2, which will be completed in the summer of 2019. In addition, it will provide data on participant preferences, acceptability, and potential barriers to the adoption of teleconsent. For phase 2, researchers partner with ongoing clinical trials and assign participants (n=64 at each site) to either consenting by teleconsent or traditional paper-based consenting. Various validated surveys will be given to participants both immediately after the consent process and 30 days postconsent to determine differences in the understanding of the consent process between groups. Moreover, surveys will be administered to the study personnel who are consenting patients throughout the process to study the additional workload and demand placed upon them. We hypothesize that there will be no significant difference in the quality of informed consent or additional workload demand placed on researchers between traditional paper-based consenting and teleconsent. With these results, we hope to increase the usage of teleconsent in clinical trials to reduce barriers to study enrollment and improve underserved groups’ participation in research.

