**Objective:**

The objective of this study is to utilize telemedicine to improve the informed consent process for clinical trials and studies. We aim to assess the feasibility and efficacy of the teleconsent intervention among residents in urban and rural settings.

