### Procedure

In phase 1, following the initial eligibility screening and identification as possible participants, interested individuals will be contacted by emails or phone to invite them to schedule a 1-hour mock consent session with a member of the study team. Before the mock consent session, participants at UNC will e-sign an Web-based consent form sent by Qualtrics and those at MUSC provide verbal consent at the time of scheduling, which is confirmed by the coinvestigator prior to participating in study procedures. During the mock consent session, study personnel will give participants a brief overview of Doxy.me and teleconsent before walking participants through a mock consent form created for this study. The purpose of the mock consent form is not to actually complete an informed consent session but to highlight the functionalities of the software. Immediately after the completion of the mock consent process, study personnel will conduct audiorecorded, semistructured interviews with participants about their experiences. After the study completion, participants will either receive cash or a gift card sent electronically or mailed to their residence(s). In total, 40 participants are to complete phase 1 of the study at each site, for a total of 80 participants between UNC and MUSC.

For phase 2, participants (n=64 at each site) will be assigned to either consenting for the clinical trial through teleconsent (n=32) or through paper-based consenting (n=32). Notably, 64 subjects per site (totaling n=128 between sites) will provide 80% power to detect modest differences (effect sizes ~0.50) between groups with respect to the survey instrument scores. After consenting for participation in the teleconsent study, participants will undergo the informed consent process using either teleconsent or traditional consent. After the completion of the consent process, participants will immediately fill out the quality of informed consent (QuIC), Decision-Making Control Instrument (DMCI, and Short Assessment of Health Literacy-English version (SAHL-E). Thirty days postconsent, participants will be asked to fill out this set of surveys once more electronically; they will be paid for each set of surveys completed.

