### Data Analysis

In phase 1, all interviews will be professionally transcribed and imported into the NVivo 12.0 (QSR International Pty, Doncaster, VIC, Australia) qualitative analysis software. Verification of the transcript accuracy will be performed prior to analyzing the text. An iterative process will be used in the analysis of the data. Then, 2 team members will code the data following its transcription by tagging segments of text in the transcripts to a concept, expanding, refining, and reducing the concepts, and discussing the findings in detail to allow for cross-validation of findings between the 2 sites [28]. A coinvestigator at MUSC with advanced training in research ethics and bioethics will explore the ethical appropriateness and associated principles of teleconsent using an integrative bioethical approach, and the MUSC research team will review emerging findings at the midpoint and conclusion of coding to consider what additional data will be necessary to refine our understanding of the participants’ perspectives related to teleconsent and determine overall themes. In addition, any feedback about the Doxy.me software will be submitted to developers at MUSC.

In phase 2, for patient participants, descriptive statistics (means, SDs, medians, etc) of responses to the survey instruments will be used to characterize the 2 groups (ie, teleconsent vs paper-based consent). Participants will be stratified with respect to demographics and clinical study. Each of the survey instrument summary scores and subscale scores will be essentially continuous variables; as such, comparisons between groups will be delineated through analysis of covariance modeling. In these models, the instrument score will serve as the dependent variable, with the experimental group serving as the key independent variable of interest. The analysis of covariance model includes participant factors, such as education and other demographics, as covariates in the models.

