For study personnel, descriptive statistics will be used to study the differences in the NASA-TLX between the 2 groups through a 2-sample *t* test of means. The sample size of the research assistant group will be based on the number of research assistants currently working on the clinical trials. Regardless, we will assume 2-sided hypothesis testing with an alpha level of.05. We suspect that the null hypothesis will display no significant difference in the means of the research assistants’ NASA-TLX scores for teleconsent versus paper-based consenting.

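### Phase 2 hypothesizes no significant difference between teleconsent and paper, but its tests and sample size are built to detect a difference, so p > .05 would satisfy the hypothesis without showing similarity

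*Protocol article*

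**What the plan says.** The hypothesis for phase 2 is in the Discussion: "We hypothesize that there will be no significant difference in the quality of informed consent or additional workload demand placed on researchers". The same paragraph goes on to hope that the results will lead to wider use of teleconsent.

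For staff workload, Data Analysis repeats the expectation: "We suspect that the null hypothesis will display no significant difference in the means of the research assistants’ NASA-TLX scores".

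The analyses are tests for a difference:

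- **Patient instruments (Data Analysis):** "comparisons between groups will be delineated through analysis of covariance modeling", with assigned group as the variable of interest and participant factors as covariates.
- **Workload (Data Analysis):** the plan is to "study the differences in the NASA-TLX between the 2 groups through a 2-sample *t* test of means", and "we will assume 2-sided hypothesis testing with an alpha level of.05".
- **Sample size (Procedure):** "64 subjects per site (totaling n=128 between sites) will provide 80% power to detect modest differences (effect sizes ~0.50) between groups". The split is 32 and 32 at each site, so 64 per arm over both sites.

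The number of research assistants is whatever the partner trials happen to have. Recruitment gives up to 10 and possibly as few as 2 at UNC. The power statement covers the patient survey scores only.

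**The concern.** A test against zero difference can give evidence that two methods differ. When it fails to reject, it gives no evidence that they are alike. Here the predicted and hoped-for outcome is the failure to reject. Anything that makes the comparison less precise (a smaller sample, noisier scores, non-response to the 30-day survey) makes that outcome more likely, so a weaker study is more likely to meet its hypothesis.

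This matters because of the intended use. Study Instruments names people with less education, mental illness or advanced age as at risk of poorer comprehension, and the Discussion hopes to extend teleconsent to underserved groups. If a real loss of comprehension were missed and reported as no significant difference, people in those groups would be among those affected.

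**Working it through.** **Inputs.** From the protocol: 64 per arm pooled and 32 per arm at one site (Procedure), standardized effect 0.50 (Procedure), two-sided alpha .05 (Data Analysis). Alpha is stated in the study-personnel paragraph and is assumed to apply to the patient scores as well. Further assumptions: independent observations, no loss, no gain in precision from covariates. Differences *d* are in SD units.

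**Step 1: reproduce the stated power.** The standard error of the difference is √(2/n).

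- n = 64: √(2/64) = 0.177. Power = Φ(0.50/0.177 − 1.96) = Φ(0.87) = 80.7%. The t-based value is 80.1%.
- n = 32: √(2/32) = 0.25. Power = Φ(0.50/0.25 − 1.96) = Φ(0.04) = 51.6%. The t-based value is 50.4%.

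The stated 80% is correct for the pooled 128 as an ordinary two-sided difference calculation. The arithmetic is sound, and it confirms which question the study was sized for.

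**Step 2: how often a real deficit gives p > .05.** This is 1 − power of the two-sample t test.

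| True deficit | 64 per arm (pooled) | 32 per arm (one site) |
|---|---|---|
| 0.5 SD | 19.9% | 49.6% |
| 0.4 SD | 38.8% | 65.0% |
| 0.3 SD | 60.9% | 78.1% |

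The one-site column is relevant because Study Setting plans comparisons within as well as across institutions.

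**Step 3: what a non-significant result leaves open.** The 95% CI half-width is 1.96 × √(2/n).

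- n = 64: 1.96 × 0.177 = 0.35 SD.
- n = 32: 1.96 × 0.25 = 0.49 SD.

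For example, an observed pooled deficit of 0.30 SD gives an interval from 0.30 + 0.35 = 0.65 SD worse to 0.35 − 0.30 = 0.05 SD better. It includes zero, so it fits the stated hypothesis, yet it does not exclude a deficit larger than the effect used for the sample size.

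**Step 4: what the planned sample could support as non-inferiority.** The document gives no margin, so a range is assumed. With true difference 0, one-sided .025 and no loss, power = Φ(margin/√(2/64) − 1.96). The n per arm for 80% power is 2 × ((1.96 + 0.84)/margin)², rounded up.

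| Margin | Power at 64 per arm | n per arm for 80% |
|---|---|---|
| 0.5 SD | 81% (t-based 80%) | 63 |
| 0.4 SD | 62% (t-based 61%) | 99 |
| 0.3 SD | 40% (t-based 39%) | 175 |

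The planned 128 gives 80% power only for a margin of about 0.5 SD, on one score.

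**Workload.** None of these figures carries over to NASA-TLX. That comparison rests on repeated forms from a handful of assistants (one form per patient, according to Procedure) and has no stated power.

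**The case against.** The strongest reply is that the design is coherent for its stated aims. Need for This Research sets out to compare the two methods and to find how far, if at all, teleconsent affects consent and workflow, and the Discussion says that the surveys serve to determine differences in understanding. Two-sided tests powered for 0.50 SD fit that. On this reading the two statements of no significant difference are predictions, and margins or interval rules belong in a fuller protocol or analysis plan that is not shown.

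Much of this stands. The tests are valid for those aims, and the absence of a margin is not itself the fault. What remains is the hypothesis wording. It is given in two places, it makes non-significance the predicted result, and it is followed by the hope of wider use. A later analysis plan could add a margin, but the published hypothesis would still be met by p > .05.

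Three stronger readings are tempting and are not supported:

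- **That the plan treats p > .05 as proof of equality.** No sentence says so. The wording leaves that route open, which is a risk and not a stated rule.
- **That the abstract adds a conflicting superiority aim.** It says: "The objective of this study is to utilize telemedicine to improve the informed consent process for clinical trials and studies". That can mean access or process, since the Introduction ties the expected gains largely to travel, time and remote personnel. It need not be a claim of better comprehension scores.
- **That 128 participants already suffice for non-inferiority.** This holds only at a 0.5 SD margin, for one patient score, with no true difference and no loss. The 0.50 in Procedure is a detectable effect and is nowhere justified as an acceptable loss.

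**Conclusion.** The concern holds as a mismatch between the phase 2 hypotheses in Data Analysis and Discussion and the tests and power planned for them. A non-significant result would satisfy the hypotheses and still be compatible with a material deficit: at 64 per arm it would occur in about two of five studies if the true deficit were 0.4 SD, and in about three of five if it were 0.3 SD. At one site the chance is even or worse for every deficit up to 0.5 SD. The figures assume two-sided .05, equal arms, no loss and no covariate gain. Useful covariates would lower the miss rates and loss to follow-up would raise them. The workload half of the point is one of logic only, because the document gives no basis for a power figure there. The planned comparisons themselves can stay.

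**What to change.** Reword the hypotheses in Data Analysis and Discussion so that no conclusion of similarity rests on p > .05. Base the conclusion on the two-sided 95% CI of the covariate-adjusted difference, in one of two ways:

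- **(a) Estimation.** State the aim as estimating the difference, which agrees with Need for This Research, and report which deficits the interval excludes. Expect a half-width of about 0.35 SD pooled and 0.49 SD per site.
- **(b) Non-inferiority.** Name one patient score, for example the QuIC objective score. Justify a margin in scale points, claim non-inferiority only if the interval excludes it, and restate the power for that margin from the second table above. A margin tighter than 0.5 SD means accepting lower power, enlarging the study or choosing (a).

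For NASA-TLX, report the difference with its interval and make no claim of equal workload from a non-significant test.

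Option (a) costs wording only, with the same sample and the same analysis of covariance. Option (b) obliges the sponsor to commit to a margin and may require more participants. Under either, some results will have to be called inconclusive where the present wording would count them as agreeing with the hypothesis.

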## Appendix

Multimedia Appendix 1 Notice of Award for Grant funding from NIH.

Multimedia Appendix 2 Summary statement and peer-review comments.

## Abbreviations

CTSA: Clinical Translational and Science Award
DMCI: Decision-Making Control Instrument
MUSC: Medical University of South Carolina
NASA: National Aeronautics and Space Administration
QuIC: Quality of Informed Consent
REDCap: Research Electronic Data Capture Platform
SAHL-E: Short Assessment of Health Literacy-English version
SUS: System Usability Scale
TLX: Task Load Assessment
UNC: University of North Carolina at Chapel
